### Objectives

This paper describes the protocol of a pragmatic randomized controlled trial (RCT), PAC-WOMAN, targeting Portuguese post-menopausal women diagnosed with hormone-receptor-positive breast cancer, currently on Aromatase Inhibitors. This project primary aims are:a) To develop and test the long-term (16-month) effectiveness and cost-effectiveness of two 4-month group-based interventions, compared to a control waiting list, on promoting sustained changes in PA, sedentary behavior, QoL, and healthcare services’ use (primary outcomes)b) To compare the effects of both interventions (i.e., brief PA counseling vs. structured exercise) on long-term changes in our primary outcomes, as well as their cost-effectivenessc) Evaluate pretreatment moderators of 4-month and 16-month changes in PA, sedentary behavior, and QoLd) Identify critical motivational (theoretical) mechanisms of change in PA, sedentary behavior, and QoL, and explore their mediating role.

As secondary aims, we will study the impact of both interventions on AI therapy continuation, adverse events of treatment, disease-free survival, body composition, sleep quality, physical parameters (e.g., muscular strength), and psychosocial factors (e.g., body image). Furthermore, process evaluation will also be conducted seeking to analyze implementation facilitators and barriers.

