#### Study design and setting

PAC-WOMAN is a three-arm, superiority parallel-group, pragmatic randomized controlled trial (RCT), comprising a 4-month intervention period and a 12-month follow-up, that will be conducted to evaluate the effectiveness of two interventions aimed at promoting active lifestyles and improved quality of life in the long-term, albeit with different approaches (brief PA counseling vs. supervised structured exercise), compared to a control group.

Clinical trials can be conceptualized across a continuum from explanatory to pragmatic, with the former assessing if a program could work under ideal circumstances and the latter determining if it could work in real world conditions. Pragmatic trials are necessary for developing and testing interventions using the settings, resources, patients, and approaches to which they will ultimately be implemented [51, 52], thus ensuring that research funds have the greatest potential to impact patient and population health and have therefore been recommended [53].

This project will be conducted under real world circumstances at a main urban center served by several hospitals. Interventions were designed to take place at local gyms, with facilitated accessibility and appropriate equipment and facilities. Recruitment of participants is taking place via dissemination of the trial in main hospitals with oncology centers. A schematic description of the study phases and participant’s timeline, according to SPIRIT, is presented in Table 1. Participants will be enrolled in cohorts or “waves”. Ethics approval was obtained prior to study development/implementation from the faculty responsible for the study (FEFD: M25C21) and all recruitment hospitals (CAML: 285/21; HFF: 10/2022; IPOLFG: UIC/1499; CHLO: 2281). The trial is being conducted in accordance to the declaration of Helsinki for human studies from the World Medical Association [54].

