#### Participants

Recruitment (ongoing) will aim for 122 Portuguese breast cancer survivors who have completed primary cancer treatment and are currently under aromatase inhibitors therapy and will subsequently be randomized to receive the brief PA counseling (PAC), the structured exercise program (StEx), or to a waiting list control group.

The inclusion criteria for entering this study are: 1) post-menopausal women, below 70 years old; 2) histologically confirmed hormone-receptor-positive breast cancer (stage I, II, III); 3) having initiated AI hormonal therapy following the primary treatment (surgery, radiotherapy, chemotherapy, etc.), at least 1 month before being enrolled; and 4) ECOG-Performance Status 0–1 (being able to perform light-to-moderate physical activities). The exclusion criteria are: 1) evidence of stage IV cancer or synchronous tumors; 2) uncontrolled hypertension, cardiac or pulmonary disease; 3) contraindications to exercise training according to the assistant doctor; 4) inability to provide informed consent; and 5) expected inability to fulfill the proposed program schedule.

Given the study design, sample size estimations were calculated for primary outcomes having one-way factorial analysis of variance with repeated measures as the reference statistical analysis. Based on previous research findings, and considering a 25% dropout, the sample size was estimated in 98 participants to detect a small to moderate effect size (α = 0.05; statistical power = 0.80) using G*Power 3.1. Consensual criteria on sample size needs for mediator/moderator analyses are not consensual and depend on the procedure and number of indicators and pathways in the models; therefore, we increased the estimated number of participants in 25%, obtaining a final estimated sample size of 122 participants.

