#### Assessments

Participants will be assessed at four time points: baseline (T_0_), 4 months (intervention’s end; T_1_), and 10 and 16 months (T_2-_T_3_; during follow-up). A schematic description of all the measurements by timepoint is presented in Table 2. Assessments will take place in standardized conditions, at the exercise setting, in a calm comfortable environment, in small groups, with a group of study technicians attending every assessment period. At each assessment point, the research staff provides participants with an accelerometer, which they are required to wear for a week, and schedules an evaluation visit to the exercise setting, where participants complete the full battery of assessments, described below, and according to the assessment plan for that timepoint. An individual report with the assessment results will be provided to each participant at the end of each assessment period is complete. Participants will be contacted close to each assessment point to determine any changes in their contact or personal information that may have occurred, especially in the fulfillment of the eligibility criteria.

**Table 2 Tab2:** Measurements’ timeline

	**Intervention**		**Follow-up**	
	**T0 Baseline**	**T1 4 months**	**T2 10 months**	**T3 16 months**

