#### Statistical methods

Factorial Anovas with repeated measures, adjusting for potential covariates (e.g., primary treatment, length of AI therapy), will be conducted for primary and secondary outcomes. The analysis will be intent-to-treat to include compliance effects in the overall assessment. Last Observation Carried Forward will be used to impute missing values. A per-protocol analysis will also be conducted without participants who do not attend at least 80% of the sessions. Normality plots and Kolmogorov–Smirnov tests will be used to test normality of outcome variables. If substantial departure from normality is found, square root log transformations will be computed. If normality is still not satisfied, non-parametric tests (e.g., Kruskal–Wallis) will be employed. As the experimental design is factorial, multiple comparison adjustments will not be appropriate.

Mediators of change, i.e., mechanisms by which participants change their lifestyle behaviors and QoL (vs. controls), will be explored using structural equation modeling (AMOS 18.0) and multiple mediation analysis (PROCESS macro v. 3.3 for SPSS). Putative candidates will include motivational (e.g., autonomous motivations) and self‐regulatory (e.g., action planning) variables. Mediation is said to occur when the causal effect of an independent variable (X) on a dependent variable (Y) is partially or fully explained by a mediator (M) [93]. Indirect effects will be tested using Preacher and Hayes’ procedures [94]. Bootstrapping with 5000 samples and 95% CI estimates for indirect effects will be calculated and assumed significant (α = 0.05) if the CI does not encompass zero [95, 96]. The ratio of the indirect effects to the total effects (P_*M*_) will be calculated to express the strength of the mediation effects [95]. Moderators, i.e., baseline characteristics that have an interactive effect with the intervention on the outcome(s), will be assessed to better understand individual differences in intervention effects [97, 98]. Moderation effects on primary outcomes will be conducted at intervention or follow-up’s end.

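### The normality rule checks outcomes instead of residuals and can replace the covariate-adjusted repeated-measures ANOVA with an unspecified rank test that does not address sustained change

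*Protocol article*

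**What the plan says.** The protocol article, Statistical methods, sets out four steps.

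- Main analysis: "Factorial Anovas with repeated measures, adjusting for potential covariates (e.g., primary treatment, length of AI therapy), will be conducted for primary and secondary outcomes".
- Check: "Normality plots and Kolmogorov–Smirnov tests will be used to test normality of outcome variables". Residuals are not mentioned.
- First response: "If substantial departure from normality is found, square root log transformations will be computed". The text does not say whether this means square root, log, or one after the other.
- Second response: "If normality is still not satisfied, non-parametric tests (e.g., Kruskal–Wallis) will be employed".

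The question to be answered is under Objectives, where the first aim is a 16-month comparison "on promoting sustained changes in PA, sedentary behavior, QoL, and healthcare services’ use (primary outcomes"). Under Assessments, "Participants will be assessed at four time points: baseline", then 4, 10 and 16 months. The sample size under Participants was calculated "having one-way factorial analysis of variance with repeated measures as the reference statistical analysis".

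**The concern.** There are two faults, and they compound.

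The check is aimed at the wrong object. ANOVA inference assumes roughly normal errors, not a roughly normal outcome. An outcome can look non-normal because a baseline characteristic is skewed, or because a score takes few values, while the model is adequate.

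The response is not tied to the question. Kruskal–Wallis compares independent groups on one value per person. It cannot carry the listed covariates or an arm-by-time term, and it returns an omnibus p-value without an effect estimate. The second aim, counselling against structured exercise, needs a contrast between two arms with a size attached.

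The rule replaces the main analysis; it is not described as a sensitivity analysis. One primary outcome could be reported from an adjusted repeated-measures model and another from an unadjusted rank test, with the choice made by a pre-test on the data.

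**Working it through.** **The plan's own figure.** The normality rule has no figure attached, but the sample size shows what the trial was sized for. With 3 arms, 4 visits, α = 0.05 and power 0.80 from the article, and f = 0.15 and correlation ρ = 0.5 assumed because neither is given, the arm-by-time test needs N = 78: noncentrality f²·N·m/(1−ρ) = 0.0225 × 78 × 4 / 0.5 = 14.04, with (3−1)(4−1) = 6 and (78−3)(4−1) = 225 degrees of freedom. Then 78 × 1.25 = 97.5, or 98, and 98 × 1.25 = 122.5 against the stated 122. So 98 is consistent with an arm-by-time test under these assumptions. The fallback is not covered by this calculation.

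**Does checking the outcome mislead?** Simulated, 90 to 120 participants, assumed distributions:

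- Skewed baseline plus exactly normal residuals: the Lilliefors version of Kolmogorov–Smirnov rejects the raw outcome in 20–23% of samples. The uncorrected version, which plugs in the estimated mean and SD, rejects in about 1%.
- Normal score rounded to 13 levels (mean 67, SD 20), as a stand-in for a coarse quality-of-life scale: Lilliefors rejects the raw score in 94% to over 99%; the uncorrected test in roughly 13–36%.

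The article does not say which version will be used.

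**How often would the switch follow?** N = 122, Lilliefors, counting a switch only if square root and log both fail:

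| Assumed outcome | Switch rate |
|---|---|
| Log-normal (log-SD 0.5 or 0.8) or gamma (shape 2) | about 1–6% |
| Gamma (shape 2) with 15% zeros, log(x+1) | about 66% |
| 13-level quality-of-life score | near 100% |

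A transformation cannot remove a spike at zero or the steps in a coarse score. The 66% depends on the Lilliefors version and on the constant added before taking logs.

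**What does the fallback lose?** Assumed normal data, arm means 0, 0.3 and 0.6 SD, one follow-up visit, 40 per arm:

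| Analysis | ρ = 0.5 | ρ = 0.7 |
|---|---|---|
| Kruskal–Wallis on follow-up value | 63% | 63% |
| Kruskal–Wallis on change score | 62% | 85% |
| Baseline-adjusted model | about 78% | about 92% |

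At 30 per arm, Kruskal–Wallis on follow-up has about 50% and the baseline-adjusted model 65% (ρ = 0.5) or 81% (ρ = 0.7).

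**Can Kruskal–Wallis be run on all visits together?** No. Stacking the three follow-up visits as if independent gave 21–28% type I error with no true effect.

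**The case against.** The case on the other side is substantial, and most of it limits the size of the point.

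- The trigger is not a bare test. Plots are also used, transformation requires a substantial departure, and the switch comes only after transformation fails. This stands. A reader might infer that skewed outcomes will usually end in Kruskal–Wallis, because a square root alone often fails (16–88% in the cases tried). But log is also named, and with both tried the rate for ordinary skew falls to about 1–6%.
- A reader might infer that outcomes will look non-normal merely because the arms differ. At plausible effects this fails: shifting one arm by 1 SD gave 4% rejection, about the nominal rate, and even 2 SD gave only about 16%.
- A reader might infer that 122 participants would be worth only 92 to 62, from a variance ratio 1/(1−ρ²) of 1.33 (ρ = 0.5) to 1.96 (ρ = 0.7). That measures follow-up-only analysis against baseline adjustment, and the article does not list the baseline outcome as a covariate. Against a two-visit change, which is nearer to the planned ANOVA, the ratio is 1/(2(1−ρ)): 1/(2 × 0.5) = 1.0 and 1/(2 × 0.3) = 1.67. At ρ = 0.5 nothing is lost in precision.
- Kruskal–Wallis is only an example. A change-score version would use baseline and keep the 5% error rate, so it is too strong to say that no rank test could speak to change. But the article does not specify that version, and it still has no covariates and no arm-by-time term.
- Healthcare use is assessed once, without a baseline (Table 2), so it has no repeated measure to lose. Costs go into a cost-effectiveness ratio, to which the normality rule is not said to apply. Neither supports the point.

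**Conclusion.** The point holds in a limited form. The article prints the rule, so this is not a detail left to a fuller document. The rule checks outcomes where residuals matter, and its only named fallback, applied to the outcome at a visit, drops the covariates, baseline, arm-by-time term and effect estimate that the sustained-change aim needs.

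The exposure is uneven. It is small for ordinarily skewed outcomes if both transformations are tried, and real for activity minutes with many zeros and for coarse, bounded quality-of-life scores. For those scores it depends heavily on the version of the Kolmogorov–Smirnov test.

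The power gap of about 15 to 30 points at 40 per arm is against a baseline-adjusted model, not against the planned ANOVA. The distributions, correlations and arm means are all assumptions and show direction and order of size only. The finding itself rests on the text. It should be corrected, but it does not undermine the trial's design.

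**What to change.** Rewrite the rule in Statistical methods before the outcome data are unblinded.

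1. For the primary outcomes measured at all four visits, keep one prespecified repeated-measures model, adjusted for the baseline value and the named covariates, with arm-by-visit terms and arm contrasts at each follow-up.
2. Judge the model by residual plots, not by tests on the raw outcome.
3. If the residuals are clearly non-normal, keep the same model and report the arm contrasts with robust or bootstrap confidence intervals. Bootstrapping is already planned for the mediation analysis.
4. Keep rank tests as sensitivity analyses only, stating the visit and whether they use the outcome or its change.
5. If a transformation is retained, say which one, for which outcome, and how zeros are handled.

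The cost is a change of wording and a little more analysis work. No data collection, visit or sample size changes.

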**Primary outcomes**				
Physical activity/sedentary behavior (objective and self-reported)	X	X	X	X
Lifestyle physically active choices	X	X	X	X
Quality of Life	X	X	X	X
Healthcare use	-	X ^a^	-	-

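### Multiplicity adjustment is ruled out because the design is called factorial, but this is a three-arm parallel trial with several unranked primary outcomes

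*Protocol article*

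**What the plan says.** Statistical methods (protocol article) plans the analysis as "Factorial Anovas with repeated measures, adjusting for potential covariates (e.g., primary treatment, length of AI therapy), will be conducted for primary and secondary outcomes" and then rules out adjustment: "As the experimental design is factorial, multiple comparison adjustments will not be appropriate".

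Study design and setting describes the design differently: "PAC-WOMAN is a three-arm, superiority parallel-group, pragmatic randomized controlled trial (RCT"). Participants and Interventions list the arms as brief counselling (PAC), structured exercise (StEx) and a waiting list. Nobody is allocated to both interventions.

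The Objectives set the comparisons. Aim (a) concerns "two 4-month group-based interventions, compared to a control waiting list". Aim (b), also primary, is "To compare the effects of both interventions (i.e., brief PA counseling vs. structured exercise) on long-term changes in our primary outcomes". The primary outcomes are given as effects "on promoting sustained changes in PA, sedentary behavior, QoL, and healthcare services’ use (primary outcomes"). Table 2 lists as primary "Physical activity/sedentary behavior (objective and self-reported"), lifestyle active choices, quality of life and healthcare use. None is ranked above the others.

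The sample size paragraph under Participants uses one alpha of 0.05.

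**The concern.** The sentence does more than leave multiplicity for later. It rules adjustment out, and the reason does not describe this trial. A factorial experiment crosses two or more treatment factors, whereas here there is one factor with three levels. The sample size paragraph mixes the terms as well, calling the reference analysis both one-way and factorial.

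The usual argument for leaving a factorial design unadjusted concerns separate treatment factors that answer separate questions. It has no bearing on how many primary outcomes are tested.

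At stake is what counts as success. The trial is labelled a superiority trial, and the Dissemination plans make scale-up conditional on the interventions proving successful and cost-effective. With several unranked outcomes, three contrasts and no adjustment, any one significant result could be offered as that proof, and the nominal 5% would not describe the risk that it is a chance finding.

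**Working it through.** **1. The plan's own figures.** The article gives no family-wise error rate. It gives alpha 0.05, power 0.80, 98 participants, then a 25% increase: 98 × 1.25 = 122.5, stated as 122. That increase is attributed to the mediator and moderator analyses, so neither alpha nor sample size allows for several primary tests.

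**2. Inputs from the article.**
- Three arms, total 122.
- Three contrasts: two with control from aim (a), one between interventions from aim (b).
- Outcomes at 16 months. Table 2 schedules healthcare use once, with a footnote placing it 6 months after the intervention starts, so it is not a 16-month outcome. Four primary entries remain if active choices is counted (PA, sedentary behaviour, active choices, quality of life), and three if it is not.

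**3. Assumptions, not in the article.** Arms of 41/41/40, two-sided 0.05 per test, and equal correlation between outcomes of 0 to 0.7.

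**4. Counting bound.** For k independent tests the chance of at least one false positive is 1 − 0.95^k.
- k = 4: 18.5%
- k = 8 (four outcomes, two contrasts): 33.7%
- k = 12 (four outcomes, three contrasts): 46.0%

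The last two overstate, because contrasts that share an arm are correlated.

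**5. Simulation allowing for shared arms** (global null, 40,000 trials, pooled-variance t tests). For one outcome: three ungated pairwise tests 12.3%, two tests against control 9.1%, pairwise tests only after a significant overall test 5.1%.

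For four outcomes:

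| Decision rule | corr. 0 | 0.3 | 0.5 | 0.7 |
|---|---|---|---|---|
| Three pairwise tests, ungated | 40.4% | 38.3% | 34.2% | 29.0% |
| Two tests against control | 31.3% | 29.9% | 26.8% | 22.4% |
| Pairwise only after overall test | 18.6% | 17.8% | 15.9% | 13.4% |

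For three outcomes, correlation 0 to 0.7: 32.1% to 25.2% ungated, 14.3% to 11.4% gated.

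The zero-correlation column can be checked by hand from the one-outcome rates: 1 − (1 − 0.123)^4 = 40.8%; 1 − (1 − 0.0913)^4 = 31.8%; 1 − 0.95^4 = 18.5%. A repeat simulation agreed to within about one percentage point.

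**6. Check of candidate remedies.** With three arms, any two of the three pairwise equalities together imply the third. The only joint hypothesis is therefore that all three arms are equal. Testing it at 0.05 and then each pair at 0.05 is a closed procedure, and it holds 5% for one outcome (simulated 4.9% to 5.1% under full and partial nulls).

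This does not extend across outcomes if a significant overall test alone opens the next outcome. Suppose one arm truly differs from two equal arms. The overall test is then rejected correctly, while the null contrast between the equal arms is still tested at 5%.
- Effect on the first of four independent outcomes only: about 1 − 0.95² = 9.75%. Simulated with a 1.5 SD effect: 9.8% in fixed order, 9.5% with Holm on the overall tests.
- Effect on all four: about 1 − 0.95^4 = 18.5%. Simulated: 18.5% and 18.6%.

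Holm over all outcome-by-contrast tests stays at about 5%.

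**The case against.** The strongest defence is that the word refers to the group-by-time analysis of variance, which is factorial in its model terms. That explains where the word came from. It does not rescue the sentence, which speaks of the experimental design, and a within-person time factor excuses neither three arm contrasts nor several outcomes.

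A second defence is that the three contrasts answer distinct aims, and adjustment across distinct comparisons in multi-arm trials is debated. That has some force for the contrasts but none for the several outcomes within each contrast.

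A third objection is that the size of the problem depends on choices the article does not state. This stands. A reader might infer that the false positive risk simply is 35% to 40%. That needs four outcomes, three ungated pairwise tests and low to moderate correlation. The article plans analyses of variance and does not say how pairwise tests follow. If they follow a significant overall test, the figure is 13% to 19% for the same four outcomes.

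A reader might also count each of the three post-baseline visits as a separate set of tests, which under an assumed between-visit correlation of 0.6 gives 63% to 71%. The documents do not support that. The repeated-measures model pools the visits, no visit-by-visit testing is planned, healthcare use is scheduled only once, and aim (a) points to 16 months.

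**Conclusion.** The concern holds as a wrong stated rule. The justification contradicts the article's own description of the design, and the primary outcomes are left without family-wise error control.

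Under the global null, the chance of at least one false positive primary claim is roughly 11% to 41%. With four outcomes and correlation 0.7 to 0 it is about 29% to 41% for three ungated pairwise tests, 22% to 32% for the two contrasts with control, and 13% to 19% if pairwise tests follow a significant overall test. With three outcomes it is about 25% to 32% ungated and 11% to 14% gated.

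The existence of inflation is secure: every scenario examined is more than twice the nominal 5%. Its exact size is not, because the correlation, the gating and the outcome count are assumptions. Counting objective and self-reported measures separately, or the quality-of-life subscales, would raise it.

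**What to change.** Delete the sentence. Name one primary variable at 16 months. The choice is the sponsor's; accelerometer-measured PA is one option. Test the three arms on it with the 2-df overall test at 0.05, and test the three pairwise contrasts at 0.05 only if that is significant. The overall test should be of the arms at 16 months, the same quantity as the contrasts, for the closed procedure to apply. Label the other outcomes secondary or exploratory.

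If several outcomes must stay confirmatory, use one of two rules:
- Holm across all primary outcome-by-contrast tests. With four outcomes the first step is 0.05/12 = 0.0042; with three it is 0.05/9 = 0.0056.
- A fixed order in which the next outcome opens only when all three contrasts on the previous one are rejected.

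A significant overall test alone must not open the next outcome, because that gives about 10% to 18% family-wise error.

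This changes wording only, with no extra patients or visits. The article provides for dated protocol updates and keeps outcome data blinded until final data entry, so the change should be made and dated before unblinding. The cost is fewer outcomes that can carry a confirmatory claim, or some power lost per contrast.
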